## Abstract

**Background/Objectives**: Heart failure with preserved ejection fraction (HFpEF) has increased in prevalence as the population ages and associated comorbidities increase. Remote ischemic preconditioning (RIPC) has been shown to provide protection against ischemic injury to the heart and other organs. Therefore, the aim of this project will be to analyse the effectiveness of RIPC in terms of arterial stiffness, endothelial function, diastolic function, and exercise capacity in patients with HFpEF. **Methods**: The PIRIC-FEp study will be a parallel, randomised controlled trial with two groups conducted at the Faculty of Nursing in Cuenca, University of Castilla-La Mancha. Individuals who are diagnosed with HFpEF and are older than 40 years, with a left ventricular ejection fraction ≥50% and a sedentary lifestyle, will be included. The exclusion criteria will include, among others, patients with noncardiac causes of heart failure symptoms, significant pulmonary disease, diabetes, peripheral vascular disease, or myocardial infarction within the previous three months. A sample size of 48 patients was estimated, with 24 for each group. Participants will be randomly allocated (1:1) to either the RIPC intervention group or the control group to evaluate the effects on arterial stiffness, endothelial function, diastolic function, and exercise capacity. Assessments will be conducted at baseline and after a three-month follow-up period. **Results**: The findings will be published in a peer-reviewed journal article. **Conclusions**: This study is important for daily clinical practice because it provides a new approach for the treatment of HFpEF patients via RIPC.

## 1. Introduction

Heart failure (HF) is a clinical syndrome with various underlying aetiologies. HF can be classified into several types on the basis of the ejection fraction (EF) range, including heart failure with reduced ejection fraction (HFrEF), characterised by an EF less than or equal to 40%, and heart failure with preserved ejection fraction (HFpEF), where the EF is greater than 50% [1]. In HFpEF, the heart is unable to supply the amount of oxygen needed by the tissues or does so only at the expense of an excessive increase in the left ventricular ejection fraction within the normal range [2,3].

HF has been described as a pandemic, affecting 64.3 million people worldwide according to the most recent data from 2017 [4]. It has an incidence of 840 cases per 100,000 people annually, a prevalence of 3.4%—a figure that is expected to rise—and an annual global mortality rate of 24% among adults [5]. In the last decade, approximately 50% of patients with HF have been diagnosed with HFpEF, which generally has a better prognosis than HFrEF [3,6]. The prevalence of HFpEF has increased in parallel with population ageing and the increase in metabolic disorders such as obesity, diabetes, and hypertension [6].

Remote ischaemic preconditioning (RIPC) is a noninvasive cardioprotective intervention involving brief cycles of limb ischaemia and reperfusion. RIPC has the potential to protect the heart and other organs from damage caused by lethal ischaemia and reperfusion in several clinical settings [7]. Evidence supports the potential of RIPC to further improve exercise capacity, cardiac function, endothelial function, and arterial stiffness [8].

Several systematic reviews and meta-analyses of randomised controlled trials (RCTs) have investigated the effects of RIPC on a range of surgical interventions, both cardiac and vascular [9,10,11,12,13,14,15,16,17,18,19,20,21,22,23,24,25,26,27], as well as other surgical procedures [28,29,30], and in patients with a history of stroke [31,32]. These reviews examined outcomes such as troponin levels [9,16,21,29,30], myocardial injury biomarkers [11,15,20], arrhythmias [15,24,26,30], myocardial infarctions [14,15,17,18,20,21,22,23,24,25,26,27,28,30], myocardial injury [23,28,30], cardiac events [14,18,29], and stroke [17,25,30,32]. Length of stay in the intensive care unit [12,17] and overall hospitalisation time [9,12,13,30] were also evaluated. However, none of these reviews assessed the effects of RIPC on exercise capacity, endothelial function, or arterial stiffness.

Despite the substantial number of clinical trials examining the effects of RIPC in various pathologies and interventions, none have been conducted in patients with HFpEF. This may be due to the complex pathophysiology of this condition, as well as the wide heterogeneity of symptoms and comorbidities [33]. Therefore, we will hypothesise that RIPC may represent an effective treatment to reduce the morbidity and mortality associated with HFpEF. Consequently, this randomised controlled trial (RCT) will be conducted with the following objectives: (1) to evaluate the efficacy of nurse-administered RIPC—a noninvasive cardioprotective intervention using cycles of limb ischemia and reperfusion—in improving arterial stiffness, endothelial function, diastolic function, and exercise capacity, and (2) to assess its impact on quality of life (QoL) and its cost-effectiveness compared with conventional treatment.

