#### 2.7.1. Primary Outcomes

Exercise capacity:-Six-Minute Walking Test (6MWT): This test will be conducted in a 30 m long corridor. The participants will walk back and forth along this section, which will be marked with cone-shaped markers placed 29 m apart, leaving 0.5 m at each end to facilitate turns. The test will be supervised by the examiner.

Endothelial function:-Carotid Intima-Media Thickness (CIMT): CIMT will be assessed via ultrasound using the Sonosite SII device, Bothell, WA, USA. CIMT is an independent predictor of future clinical events such as myocardial infarction and sudden cardiac death [40] and allows for the assessment of structural changes over time, facilitating the monitoring of atherosclerosis [41].

Arterial stiffness:-Pulse wave velocity (PWV), the radial augmentation index (rAIx), and the central augmentation index (cAIx): These measurements will be obtained via the SphygmoCor System (AtCor Medical Pty Ltd., West Ryde, NSW, Australia) while the patient is lying in a supine position. Pulse waves will be recorded from the carotid and femoral arteries. The rAIx is calculated as follows: (Second systolic peak [SBP2] − Diastolic blood pressure [DBP]) divided by (First systolic peak − DBP), multiplied by 100 (%). The cAIx is calculated as follows: central pulse pressure augmentation times 100 divided by pulse pressure. All indices will be derived directly from the respective devices.

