### 2.9. Sample Size Calculation

The sample size was calculated using Epidat 4.2 software, which is based on the data reported by Maxwell et al. [42]. To achieve 90% statistical power and a significance level of 0.05, a sample size of 20 patients per group is needed to detect a statistically significant difference in flow-mediated dilatation. Assuming a 20% dropout rate, the final sample size is estimated at 48 participants (24 in each group).

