## 4. Discussion

The main aim of this study was to evaluate the effectiveness of RIPC in patients with HFpEF by assessing its impact on arterial stiffness, endothelial function, diastolic function, and exercise capacity. The secondary objectives are as follows: (1) To compare the effectiveness of RIPC on QoL in patients with HFpEF and (2) to analyse the cost-effectiveness of RIPC versus conventional treatment in patients with HFpEF.

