### 4.5. Physiological Mechanisms of RIPC

RIPC contributes to the optimisation of mitochondrial function by increasing ATP synthesis, improving mitochondrial respiratory efficiency, reducing the opening of the mitochondrial permeability transition pore (mPTP), and decreasing the production of reactive oxygen species (ROS) [49]. Furthermore, it has been associated with improved vascular endothelial function and an increased release of nitric oxide, facilitating a reduction in both cardiac preload and afterload [50]. Additionally, evidence suggests that RIPC-induced mitochondrial improvement in T lymphocytes may protect the myocardium by exerting anti-inflammatory effects and mitigating ischaemia-reperfusion injury-related damage [51].

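### Diastolic function is a main aim with no listed outcome, and endothelial function rests on CIMT alone while the trial is sized on a measure it does not list

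*Protocol article*

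**What the plan says.** Three places state the main aim in the same four domains. The Abstract sets out "to analyse the effectiveness of RIPC in terms of arterial stiffness, endothelial function, diastolic function, and exercise capacity in patients with HFpEF". Objective 1 in the Introduction speaks of efficacy "in improving arterial stiffness, endothelial function, diastolic function, and exercise capacity". The Discussion restates the aim "by assessing its impact on arterial stiffness, endothelial function, diastolic function, and exercise capacity". Quality of life and cost-effectiveness are kept apart as the second objective.

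Section 2.7.1 arranges the primary outcomes by domain and gives three:

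- Exercise capacity: "Six-Minute Walking Test (6MWT): This test will be conducted in a 30 m long corridor".
- Endothelial function: "CIMT will be assessed via ultrasound using the Sonosite SII device", with the explanation that this measure "allows for the assessment of structural changes over time, facilitating the monitoring of atherosclerosis".
- Arterial stiffness: pulse wave velocity and the radial and central augmentation indices.

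Section 2.7.2 lists everything else under covariates, including the quality-of-life questionnaires that serve the second objective.

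Section 2.9 bases the sample size on another variable: 20 patients per group, at 90% power and a 0.05 significance level, to "detect a statistically significant difference in flow-mediated dilatation".

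**The concern.** An aim stated three times should lead to a variable that is measured at baseline and at three months. For diastolic function the document gives none. Run exactly as listed, the trial would have no data on one of its four main questions, although section 4.2 is devoted to cardiac function and the Conclusions present improvement in cardiac function as part of what the research targets.

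For endothelial function the difficulty is one of construct. The listed measure is described in structural terms. The mechanism in section 4.5 is functional ("improved vascular endothelial function and an increased release of nitric oxide"), and so is the dilatation measure used for sizing. A null CIMT result at three months could be read as evidence against the vascular mechanism, and a chance positive as support for it, when the article's own description of CIMT supports neither reading.

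The gap also leaves room to choose a diastolic index or a dilatation measure after data have been seen. That matters more here because the outcome assessors are not blinded (section 2.7).

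**Working it through.** **Step 1. Match each main objective to the listed measures.** The inputs are the aims (Abstract, Introduction, Discussion) and every item in sections 2.7.1 and 2.7.2.

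| Main objective | Listed outcome | Does it fit by the article's own description? |
|---|---|---|
| Exercise capacity | 6MWT | Yes |
| Arterial stiffness | PWV, rAIx, cAIx | Yes |
| Endothelial function | CIMT only | Filed under this heading, but described as structural |
| Diastolic function | None | No measure to assess |

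Objectives with any listed outcome: 3 of 4. Objectives whose listed outcome is not described as something else: 2 of 4. CIMT is 1 of the 5 primary measures (6MWT, CIMT, PWV, rAIx, cAIx).

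**Step 2. Look for a diastolic measure elsewhere in the methods.** The covariates cover sociodemographics, medical history, anthropometry, blood pressure, handgrip, activity tracker, biochemistry, genotyping, and questionnaires on activity, fitness, diet and quality of life. None is an echocardiographic index or a measure of filling pressure. The biochemistry panel has no natriuretic peptide, although Table 1 uses natriuretic peptides for diagnosis. In section 2.7 the word diastolic occurs only for blood pressure, in the augmentation-index formula. Within the methods and Table 1, left ventricular diastolic dysfunction appears only in the diagnostic inclusion criterion. Section 2.10 fits ANCOVA to each outcome with its baseline value as covariate, and no listed variable would supply a diastolic model.

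**Step 3. Look for flow-mediated dilatation.** It occurs in section 2.9 and nowhere in section 2.7.

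**Step 4. Try to reproduce the stated sample size.** The inputs from section 2.9 are 20 per group, 90% power, alpha 0.05 and 20% dropout. No difference or SD is given and sidedness is not stated, so the 20 cannot be reproduced. It can be inverted. With the normal approximation, two-sided:

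d = √[2(1.960 + 1.282)² / 20] ≈ 1.03

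The exact t-test gives about 1.05, and a one-sided test (normal approximation) about 0.93. For dropout, 20 / (1 − 0.20) = 25 per group, or 50 in total. The stated 24 per group equals 20 × 1.2. The totals differ by 2 patients, and nothing here turns on that.

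**Step 5. What this N means for an outcome that is listed.** The document gives no effect size or SD for any of the five primary measures, so no corrected N can be computed. Purely as an illustration, with assumed standardised differences and an unadjusted two-sided t-test on 20 completers per group:

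| Assumed standardised difference | Power |
|---|---|
| 0.3 | 15% |
| 0.5 | 34% |
| 0.8 | 69% |
| 1.05 | 90% |

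The 90% in section 2.9 therefore carries over to a listed outcome only if the effect on it is about as large as the one assumed for dilatation.

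**The case against.** The strongest defence is that this is a condensed article whose flow figure, covering baseline and post-intervention testing, is not visible here. A diastolic index and flow-mediated dilatation may both be measured and simply have been left off the list. That possibility stands, and it is why the fix is conditional. It does not remove the point. Section 2.7 goes down to corridor markings, scale models and blood-draw times and is organised by domain, so leaving out the measure for a main aim contradicts the stated aim and is more than abridgement. Either the list or the aim is wrong.

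Three further limits are accepted.

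- A reader might infer that two of the four main objectives cannot be answered. The document does not support that count. Endothelial function has a named primary outcome under its own heading, and only diastolic function has nothing.
- A reader might go on to say that CIMT tells us nothing about endothelial function. The article describes CIMT as structural but does not call it unsuitable as an endothelial marker. A flat exclusion would need outside vascular evidence.
- The contrast between structure and function should not be overdrawn. Nitric oxide is mentioned in section 4.5 and not in section 4.3, which describes endothelial dysfunction partly as a loss of microvascular density. Likewise, diastolic function is discussed in sections 4.2 and 4.4. It is the methods that lack it.

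**Conclusion.** The point holds in two parts of unequal weight. First, 1 of 4 main objectives, diastolic function, has no listed outcome; this is a direct internal contradiction. Second, the endothelial objective depends on one measure that the article describes as structural, and the functional measure that justifies the sample size is not listed as an outcome. As listed, that measure does not support a claim about endothelial function, which is a narrower statement than saying the objective is impossible to address.

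The conclusion assumes that section 2.7 is the complete list of what will be measured. If either missing measure is in fact recorded at both visits, the corresponding part becomes an error in the list and not a gap in the data, but the text still needs correcting. The power figures in the working are illustrations on assumed effects and are not estimates for this trial.

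**What to change.** Reconcile the Abstract, objective 1, section 2.7, section 2.9, the Discussion aim and the Conclusions before any outcome data are analysed.

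1. **Diastolic function.** If an index is already recorded at baseline and three months, name it in section 2.7 at a tier consistent with a main aim; calling it secondary would leave a mismatch. If none is recorded, remove diastolic function from the aims and the cardiac-function claim from the Conclusions.
2. **Endothelial function.** If flow-mediated dilatation is already measured, list it as the outcome for this objective, which also reconnects section 2.9 to the outcome list. If it is not, report CIMT as carotid structure and draw no conclusion about endothelial function from it.
3. **Sample size.** If dilatation is not measured, restate the size and power statement for an outcome that is listed, giving the assumed difference and SD. If 48 is kept for practical reasons, say so and give the difference that 20 completers per group can detect.

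No new procedure is needed. The cost is narrower claims, plus an amendment to the protocol and the registry entry. Because aims and possibly a primary outcome would change in a registered, ethics-approved trial, this is a substantive amendment and should be handled as one.

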## 2. Materials and Methods

### 2.1. Design

The PIRIC-FEp study will be a 2-arm, parallel-group RCT evaluating an RIPC intervention in patients with HFpEF over a 3-month period. The design of this study allows for the evaluation of the effectiveness of the therapeutic intervention and minimises selection bias. By including two parallel groups, one intervention group and one control group, treatment crossover is avoided, and the internal validity of this study is reinforced, facilitating a direct and reliable comparison between the two groups. This RCT protocol has been registered on ClinicalTrials.gov (NCT07024810).

### 2.2. Setting

Patient recruitment for this RCT will be performed in the primary healthcare centres of Cuenca, as well as in the cardiology and internal medicine services of the Virgen de la Luz Hospital of Cuenca, belonging to the Castilla-La Mancha Health Service (SESCAM). Healthcare professionals from these centres and services will be informed of the trial aims to support the recruitment of eligible HFpEF patients. These patients are subsequently invited to participate in the RCT through information sessions, posters, media announcements, and referrals from healthcare professionals.

### 2.3. Participants

Patients diagnosed with HFpEF in accordance with the 2021 ESC guidelines [34] will be eligible for inclusion. The inclusion and exclusion criteria are presented in Table 1.

### 2.4. Randomisation

Participants will be randomly assigned (1:1) via EPIDAT version 4.2 software (Figure 1) to one of two groups: Group 1, RIPC; Group 2, the control group (CG). Prior to randomisation, screening will be performed, and all participants will be required to sign the informed consent form.

### 2.5. Intervention

#### 2.5.1. Remote Ischaemic Preconditioning (RIPC)

Participants randomised to the RIPC intervention group will be provided with a portable blood pressure monitor (Welch Allyn DuraShock™ DS45, Skaneateles Falls, NY, USA) to perform the RIPC procedure themselves. The cuff will be positioned on the upper arm and inflated to 220 mmHg for 5 min, followed by 5 min of deflation. This sequence will be repeated three additional times. The procedure will be performed five days per week for a period of three months. The RIPC will be applied to the left arm (with the exception of any condition that prevents it, in which case it will be performed on the right arm). The participants will be supervised during their first RIPC session and every 15 days thereafter to ensure proper administration. Participants will be allowed to carry out the RIPC procedure at any time during the day and will document each session in a diary to track adherence. They will be advised to continue with their regular daily activities and avoid starting new exercise routines or making changes to their diet. In the event of any adverse effects, such as pain, tissue damage [37], haematomas [37,38], numbness or paraesthesia [39], acute deep vein thrombosis, or acute ischaemia of the upper limb [38], the guidelines outlined in Table S1 will be followed.

#### 2.5.2. Control Group

Participants randomly assigned to the RIPC intervention group will receive a hand-held blood pressure monitor.

Each participant in the CG will be instructed to continue with their usual routine and avoid engaging in any new physical activities or dietary changes.

#### 2.5.3. Duration of the Intervention

The intervention period will span three months. Figure 2 presents the flowchart detailing patient inclusion and follow-up steps, including screening, eligibility criteria, randomisation, baseline assessments, and evaluations after the intervention.

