### 2.7. Outcomes

All outcomes will be collected and assessed by registered nurses who are members of the research team; however, they will not be blinded, as they will also be responsible for monitoring compliance and instructing patients on the application of the RIPC.

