### 2.11. Mitigation Strategies

Heterogeneity among participants.
○To reduce heterogeneity among participants, the established inclusion and exclusion criteria will be rigorously applied, thereby ensuring a more homogeneous sample.

Dropouts and missing data
○Qualified nursing staff from the research team will be responsible for training participants in the correct application of the therapy, as well as monitoring follow-up diaries and providing reminders via weekly phone calls and biweekly visits to ensure adequate compliance and minimise losses during follow-up. In addition, analyses will be conducted according to the intention-to-treat principle, meaning that all participants will be included in the primary analysis, regardless of whether or not they complete the intervention. With respect to the treatment of missing data, appropriate statistical methods, such as imputation techniques, can be applied to reduce the bias associated with missing information.

Small sample size.
○Although the sample size is small, it has been calculated on the basis of previous estimates and a dropout rate of 20%, which has been incorporated into the calculation to ensure the minimal statistical power required to detect relevant effects.

Exercise tolerance may be influenced by participants’ daily activities.
○Participants will be instructed to maintain their usual lifestyle during their involvement in this study. To monitor this, measurements will be taken via activity trackers, the 6MWT, and self-reported physical activity questionnaires.

Lack of blinding.
○The absence of blinding in both participants and research staff could influence the subjectivity of some assessments. To mitigate this limitation, objective measures, such as anthropometric parameters, blood pressure, biochemical markers, muscle strength tests, and exercise capacity assessments, among others, will be included. Similarly, to reduce bias resulting from the lack of blinding in the research team, standardised protocols for data collection will be applied.

Potential bias.
○To mitigate potential bias, confounding variables such as medication, age, sex, and socioeconomic status will be considered in the analyses.

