### 4.6. Potential Limitations

Some potential limitations of this study must be considered: (1) this study will be conducted with individuals from a single province (Cuenca), which limits the generalisability of the findings to the broader population; (2) although the proposed sample size is not very large, it may not be fully achieved, which would reduce the statistical power of this study; (3) the intervention will be carried out by the participants themselves following prior instructions provided by a healthcare professional. This could lead to errors in implementation and difficulties in monitoring adherence, potentially affecting the effectiveness of the RIPC. (4) The intervention will last three months, so even if effects are observed at the end of this period, they could be temporary. Therefore, longer-term studies will be necessary to assess the long-term effect of the RIPC; and (5) the absence of blinding in participants can affect subjective assessments, such as self-report questionnaires, and favour the emergence of biases associated with the placebo effect. For its part, the lack of blinding of the research team, in addition to affecting subjective assessments, could influence the way in which data are collected, recorded, or interpreted, thereby jeopardising the objectivity of this study.

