**Figure 2 biomedicines-13-01923-f002:**
[figure not shown]
Flowchart for patient inclusion and follow-up: screening, inclusion and exclusion, randomisation, baseline testing, and postintervention testing.

**Table 1 biomedicines-13-01923-t001:** Inclusion and exclusion criteria.

Inclusion Criteria	Exclusion Criteria
**1. Diagnosis of HFpEF (according to 2021 ESC criteria):** **Signs and symptoms of HF** **Left ventricular ejection fraction (LVEF) ≥ 50%** **Objective evidence of structural and/or functional cardiac abnormalities consistent with left ventricular diastolic dysfunction and/or elevated left ventricular filling pressures, including elevated natriuretic peptides** **2. Sedentary people (men and woman) (structured exercise <2 × 30 min/week)** **3. Age ≥ 40 years** **4. Written informed consent** **5. Clinically stable for at least 6 weeks** **6. On optimal medical therapy for ≥6 weeks**	1. Noncardiac causes of HF symptoms: - Significant valvular or coronary artery disease - Uncontrolled hypertension or arrhythmias - Primary cardiomyopathies 2. Significant pulmonary disease (FEV1 < 50% predicted, GOLD stage III–IV) 3. Inability to exercise or conditions that may interfere with the exercise intervention 4. History of myocardial infarction in the past three months 5. Patients with diabetes and/or peripheral vascular disease * 6. Signs of ischaemia during maximal cardiopulmonary exercise testing 7. Comorbidities that may affect 1-year prognosis 8. Enrolment in a different clinical study

ESC: European Society of Cardiology. HF: Heart failure. HFpEF: Heart failure with preserved ejection fraction. FEV1: Forced expiratory volume in 1 s. GOLD: Global Initiative for Chronic Obstructive Lung Disease. * Exclusion criterion 5 specifies that patients with diabetes and/or peripheral vascular disease were excluded. In the case of type 2 diabetes, this decision was based on evidence indicating that RIPC does not consistently confer cardioprotective effects in this population. This limitation is attributed to mitochondrial dysfunction caused by elevated levels of glycosylated proteins in diabetic patients, which interferes with the protective mechanisms typically activated by RIPC [35]. With regard to peripheral vascular disease, patients were excluded because the application of RIPC is contraindicated due to the risk of local ischaemia or tissue damage in the affected limbs [36].

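### The stated participant flow puts randomisation before baseline testing in an unblinded trial, so the baseline used in the ANCOVA and in change from baseline is open to knowledge of the arm

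*Protocol article*

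**What the plan says.** **Order of steps.** Section 2.5.3 describes the flow as "screening, eligibility criteria, randomisation, baseline assessments, and evaluations after the intervention". The Figure 2 caption reads "screening, inclusion and exclusion, randomisation, baseline testing, and postintervention testing". Section 2.4 states: "Prior to randomisation, screening will be performed, and all participants will be required to sign the informed consent form". It does not mention baseline measurement as a step before randomisation.

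**Who measures, and what they know.** Section 2.7 says: "All outcomes will be collected and assessed by registered nurses who are members of the research team". Of these nurses it adds that "they will not be blinded, as they will also be responsible for monitoring compliance and instructing patients on the application of the RIPC". Section 2.11 confirms that participants are unblinded too: "The absence of blinding in both participants and research staff could influence the subjectivity of some assessments". For the 6MWT, a primary outcome, section 2.7.1 notes: "The test will be supervised by the examiner".

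**Use of the baseline.** Section 2.10 fits an ANCOVA for each outcome, adjusted for its baseline value and for medication, age, sex and socioeconomic status. Results are presented as absolute change from baseline. The first analysis phase checks whether randomisation produced comparable groups. A propensity-score-matched sensitivity analysis addresses imbalance in baseline covariates.

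**What is acknowledged.** Section 4.6 accepts that an unblinded team "could influence the way in which data are collected, recorded, or interpreted". Section 2.11 offers objective measures, among them exercise capacity, and standardised data collection as mitigation. Neither section mentions the order of baseline testing and allocation.

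**The concern.** ANCOVA gives an unbiased treatment comparison when the baseline covariate cannot have been affected by treatment assignment. Measuring it before the allocation is known guarantees this. The stated order removes that guarantee, because in an open trial both the patient and the nurse may know the arm at the baseline test.

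The 6MWT is the most exposed outcome: the distance walked depends on the patient's effort and on how the examiner conducts the test. The self-report questionnaires are exposed in a similar way.

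A baseline recorded too low in one arm makes that arm appear to improve more. Adjusting for baseline does not remove this, because the adjustment itself uses the distorted value. The comparability check cannot help either, since it cannot separate a chance imbalance from one produced by measurement. Matching on such a baseline would carry the same distortion. Unlike the lack of participant blinding, this exposure is avoidable in an open trial.

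**Working it through.** The article gives no figure on this point to reproduce. The check has two parts.

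**1. The statements side by side**

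| Place | What comes before baseline testing | Rule on when the allocation is disclosed |
|---|---|---|
| Section 2.5.3 | Screening, eligibility, randomisation | None |
| Figure 2 caption | Screening, inclusion and exclusion, randomisation | None |
| Section 2.4 | Not addressed; screening and consent precede randomisation | None |

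No section places baseline testing before randomisation or says that the arm is concealed until it is done.

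**2. How a baseline shift passes into the estimate**

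Inputs:
- 20 evaluable patients per arm (section 2.9).
- Two-sided 5% test. The 0.05 is in sections 2.9 and 2.10; two-sided is my assumption.
- Shift b in the recorded RIPC-arm baseline, in SD units: assumed.
- Baseline to follow-up correlation r, with equal SDs at both times: assumed.
- No true treatment effect.

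The adjusted difference is (difference in follow-up means) − slope × (difference in recorded baseline means). With no true effect the first term averages zero. With equal SDs the slope is about r. Hence

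bias ≈ −r × b.

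Using change from baseline as the dependent variable with the same baseline covariate leaves the treatment coefficient unchanged, so the same formula holds. An unadjusted change score would carry the full shift, −b.

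For RIPC baselines recorded 0.2 SD low (b = −0.2):
- r = 0.5: 0.5 × 0.2 = 0.10 SD
- r = 0.7: 0.7 × 0.2 = 0.14 SD
- r = 0.9: 0.9 × 0.2 = 0.18 SD

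These can be set against the approximate standard error of the adjusted difference, √[(2/20)(1 − r²)]:
- r = 0.7: √(0.1 × 0.51) = 0.226, so bias/SE = 0.14/0.226 = 0.62
- r = 0.9: √(0.1 × 0.19) = 0.138, so bias/SE = 0.18/0.138 = 1.31

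A simulation of the ANCOVA (20 per arm, baseline as the only covariate, 20,000 runs per setting, no true effect) agrees with the formula:

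| r | Recorded RIPC baseline shift (SD) | Simulated bias (SD) | −r × b | Type I error |
|---|---|---|---|---|
| 0.5 | 0 | 0.001 | 0 | 0.051 |
| 0.5 | −0.2 | 0.097 | 0.10 | 0.061 |
| 0.7 | 0 | −0.001 | 0 | 0.052 |
| 0.7 | −0.1 | 0.068 | 0.07 | 0.060 |
| 0.7 | −0.2 | 0.142 | 0.14 | 0.092 |
| 0.9 | 0 | 0.002 | 0 | 0.052 |
| 0.9 | −0.1 | 0.090 | 0.09 | 0.093 |
| 0.9 | −0.2 | 0.182 | 0.18 | 0.241 |

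The rows with zero shift represent a baseline measured before the arm is known: bias is near zero and the test holds its level. A shift in the other direction gives the same bias against RIPC.

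**The case against.** **The order may be only a summary.** Section 2.5.3 and the caption both describe Figure 2, which is not visible in the text at hand. They are therefore not two independent statements, and neither is worded as a procedural rule. Section 2.4 says that screening and consent come first, not that nothing else does. This stands, and it limits the point to what the stated order permits. It does not remove the need to correct the text, because the order is the same in both places and nothing in the article qualifies it.

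**Lack of blinding is already disclosed.** Sections 2.7, 2.11 and 4.6 say so openly, and section 2.11 adds standardised data collection. Unblinded assessment at three months is therefore an acknowledged limitation and not the point here. The order of baseline and allocation is not among the disclosed limitations.

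Some stronger readings are tempting, but the article does not support them:
- *Baseline is measured with the arm known.* Nothing says when staff and participants learn the allocation, so this is possible but not established.
- *Patients who withdraw between allocation and baseline necessarily drop out of the ANCOVA, against intention to treat.* Section 2.11 says that all participants enter the primary analysis and that imputation can be applied. That wording is loose, but it does not imply exclusion. No interval between allocation and baseline is stated either.
- *All primary outcomes are equally exposed.* The effort argument applies to the 6MWT. Section 2.7.1 says the indices are derived directly from the devices, and no comparable effort mechanism is evident for pulse wave velocity (PWV) or carotid intima-media thickness (CIMT).
- *The false-positive rate will be inflated by a known amount.* The type I errors above follow from an assumed shift, direction and correlation. They show sensitivity and are not a forecast.

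**Conclusion.** The point holds as a weakness in the stated order of procedures. As written, randomisation precedes baseline testing, nothing keeps the arm concealed until baseline is complete, and participants and assessors are unblinded. Baseline values, above all the 6MWT, can therefore be influenced by knowledge of the arm, and the planned analysis would pass that influence on.

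The size is about r × shift, in either direction: 0.14 to 0.18 SD for an assumed shift of 0.2 SD and r of 0.7 to 0.9. The article gives neither input, and it does not show that a shift will occur. The case for acting is that the exposure can be removed cheaply before enrolment, whereas a baseline taken with the arm known cannot be retaken afterwards.

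**What to change.** State in sections 2.4 and 2.5.3 and in Figure 2 that the baseline outcome assessments (6MWT, CIMT, PWV, the radial and central augmentation indices, and the questionnaires) are completed and recorded before the allocation is generated and disclosed to participant or nurse. If this is already the practice, correct the order in section 2.5.3 and in the Figure 2 caption.

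**Cost.** No additional measurements are needed, but allocation waits until baseline testing ends. If the activity tracker, worn for 9 days (section 2.7.2), counts as baseline, the wait is more than a week. The text should therefore say whether the tracker period belongs to the assessments that must precede allocation.

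**Optional, not part of the required fix.** Where the current team allows it, a nurse who did not train or monitor the participant could run the three-month tests. The article does not give the number of nurses, so feasibility cannot be judged from it. Some participants would reveal their arm in any case. Reordering protects the baseline only; the disclosed limitation at three months remains.
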